
**Fig. 2 Fig2:**
[figure not shown]
Standard Protocol Items: Recommendations for Interventional Trials (SPIRIT) chart of the enrolments and assessments during randomized controlled trials. The “X” refers to what is done in the given period. Abbreviations: IBD, inflammatory bowel disease; WK, week

To assess dietary intakes throughout the study, we will fill 3 1-day dietary recalls (including two working days and a non-working day) at weeks 2, 3, and 4 of intervention by telephone interview. Dietary recall format is presented in Supplementary file, section B. To complete the dietary recalls, participants will be asked to report dietary intakes based on household measures. Then, we will convert household measures to grams using available booklets. The average of dietary intakes in these 3 days will be considered as participants’ dietary intakes throughout the intervention. To obtain nutrient intakes on the basis of these food recalls, we will use Nutritionist IV software (based on US National Nutrient Databank) modified for Iranian foods.

In addition, 2 1-day physical activity records (including a working day and a non-working day) will be gathered from all patients at weeks 2 and 4 of intervention to assess physical activity during the study. The format of physical activity record is shown in Supplementary file, section C. All participants will be educated how to record their activities throughout the study before the start of the trial. Furthermore, patients in both groups will be asked not to change their physical activity throughout the trial.

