### Statistical analysis

The Kolmogorov-Smirnov test will be used to examine normal distribution of variables. Log transformation will be conducted for the non-normally distributed data. To examine differences in qualitative variables between soy milk and control groups, we will use the chi-square test. We will apply the independent sample *t* test to detect differences in quantitative variables between the soy milk and control groups. In addition, mentioned test will be used to compare between-group changes in outcome variables. To do within-group comparison, we will use the paired-sample *t* test. Multivariate analysis of covariance (ANCOVA), as a general linear model, will be used to examine the effects of soy milk consumption on outcome variables. In this analysis, baseline value of outcome variables and potential confounding variables which are different between the intervention and control groups will be adjusted to avoid potential risk of bias and detect independent results. All statistical analyses will be done using the SPSS software version 18 (SPSS, Inc. Chicago, IL, USA). *P* < 0.05 will be considered significant.

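### Beyond the baseline outcome, ANCOVA covariates are chosen by observed between-arm difference and are not limited to pre-randomisation variables, so diet recorded on treatment could enter the model and absorb part of the soy milk effect

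*Protocol article*

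**What the plan says.** The Statistical analysis section of the protocol article describes the ANCOVA adjustment in one sentence, which names the baseline value of the outcome and continues: "potential confounding variables which are different between the intervention and control groups will be adjusted to avoid potential risk of bias". The baseline outcome is thus a fixed term, and every other covariate is conditional on an observed difference. The section does not list the candidates, define when a variable counts as different, or confine the choice to baseline variables. It does supply tests that could serve as the screen: a t test "to detect differences in quantitative variables between the soy milk and control groups", and for categorical data, "To examine differences in qualitative variables between soy milk and control groups, we will use the chi-square test". The only threshold is the general one, P "< 0.05 will be considered significant".

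Under Study design and intervention (text after Fig. 2), diet is recorded "at weeks 2, 3, and 4 of intervention by telephone interview", and "The average of dietary intakes in these 3 days will be considered as" each participant's intake over the intervention. Activity records "will be gathered from all patients at weeks 2 and 4 of intervention to assess physical activity during the study". No baseline measurement of either is described. The same section uses the recalls to help assess soy milk compliance, so they contain the intervention. It also names the matching factors (age, gender, BMI, type of medicines), which the analysis section does not mention as covariates.

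**The concern.** In a randomised trial, baseline differences between arms arise by chance. What makes a covariate worth including is its relation to the outcome, and a between-arm test does not measure that. A screen on imbalance therefore tends to leave out prognostic variables that happen to be balanced. The matching factors are the likeliest to be dropped, because matching makes them the least likely to differ.

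The more serious issue is timing. A variable measured during treatment may differ because treatment changed it. If soy milk raises a nutrient and that nutrient passes the screen, the ANCOVA holds constant something the intervention produced. Any part of the effect carried by that nutrient is removed from the estimate. Even if it carries none, its correlation with treatment widens the standard error. The Discussion offers the fibre and protein of soy milk as the route to a benefit, so this is the pathway the trial is meant to detect.

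**Working it through.** **Design inputs (Sample size calculation).** Means 424 and 602 μg/g, SD 141, multipliers 1.96 and 0.842. Effect = (602 − 424)/141 = 178/141 = 1.26 SD. n = 2 × (1.96 + 0.842)² × 141² / 178² = 9.85, so 10 per group. Multiplying by 1.5 for drop-out gives the stated 15 (that inflation is a separate matter). The checks below use 15 per arm unless stated.

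**Assumptions, none of them given in the protocol.** The screen is P < 0.05; the baseline outcome correlates 0.5 with the final outcome; the number and strength of candidate covariates, the nutrient shift and the share of effect it carries are varied.

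**Step 1. How often the model changes by chance.** For k independent baseline candidates, P(at least one differs) = 1 − 0.95^k:
- k = 5: 23%
- k = 10: 40%
- k = 20: 64%

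**Step 2. Screening true baseline covariates.** All models contain the baseline outcome.
- One extra covariate correlated 0.3–0.5 with the outcome, adjust-if-different against always-adjust: power about 0.85 against 0.87–0.94 at 1 SD, and 0.97–0.98 against 0.97–1.00 at 1.26 SD (simulation error about 0.01).
- Ten candidates, no treatment effect: type I error 0.037–0.052 with the screen, 0.047–0.053 with the baseline outcome alone.
- Ten candidates jointly explaining 30% of outcome variance, effect 1.26 SD: power 0.955 with the screen against 0.967 with the baseline outcome alone at 15 per arm, and 0.803 against 0.853 at 10 per arm.

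**Step 3. An on-treatment nutrient shifted by s SD: selection and standard error.** Selection is the power of the two-sample t test with 15 per arm. The large-sample SE ratio is √(1 + s²/4); the simulated ratio at this sample size is slightly higher. Both assume that the nutrient carries none of the effect.

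| s | Selected | √(1 + s²/4) | Simulated SE increase if adjusted |
|---|---|---|---|
| 0.5 | about 27% | 1.03 | about 5% |
| 1 | about 75% | 1.12 | about 15% |
| 2 | about 100% | 1.41 | about 47% |

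**Step 4. The estimate when the nutrient carries part of the effect.** Total effect 1.26 SD, s = 1 to 2, nutrient entered when it differs. With the baseline outcome only, the mean estimate is about 1.26 SD and power 0.96–0.97.

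| Share carried | Mean estimate (SD) | Fraction of total | Power |
|---|---|---|---|
| 0% | 1.25–1.27 | about 100% | 0.73–0.91 |
| 25% | 0.95–0.98 | 75–78% | 0.52–0.77 |
| 50% | 0.63–0.72 | 50–57% | 0.30–0.72 |

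**Step 5. What the protocol's one nutrient figure implies.** Fibre is given as 0.6 g per 100 g. At an assumed density of 1 g/mL, 250 mL supplies 0.6 × 2.5 = 1.5 g/day. A shift of s SD then requires a between-person SD of 1.5/s: 3 g/day for 0.5 SD, 1.5 g/day for 1 SD, 0.75 g/day for 2 SD. The protocol reports no SD for any nutrient.

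**The case against.** **The model is not wholly data-driven.** The baseline outcome, often the strongest single predictor, is always included. This stands, and it is why the power loss in Step 2 is modest.

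**Diet and activity are not named as covariates.** A reader might infer that the plan intends to adjust for them. The text does not say so: it speaks only of potential confounders, and gives the recalls and records the purposes of describing intake, activity and compliance. They are eligible because nothing excludes them, which makes the risk conditional. For physical activity it is weaker still, since participants are asked not to change it and nothing suggests that soy milk would.

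**The screen does not inflate type I error.** A reader might expect that selecting covariates from the data does so. For baseline covariates the simulations show that it does not.

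**Large nutrient shifts have no source.** This also stands. For fibre, a 2 SD shift would need a between-person SD of only 0.75 g/day, so the upper rows of Steps 3 and 4 illustrate and do not predict.

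**Adjusting for a chance imbalance can be sensible.** It can, if the variable is prognostic. That argues for naming prognostic variables beforehand; the size of the imbalance does not establish prognosis.

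**A separate analysis plan may hold the details.** It may list covariates, but the protocol has not left the matter open. It states a selection rule, and a fixed list would have to replace that rule.

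**Conclusion.** The point holds in limited form. The selection rule for covariates other than the baseline outcome is poorly chosen, and it lacks a restriction to variables measured before randomisation. Applied only to baseline covariates, it makes the model vary from sample to sample and costs little to moderate power, with no excess of false positives. The material risk is that an on-treatment nutrient raised by soy milk enters as a confounder. For assumed shifts of 1–2 SD, the standard error rises by about 15–47% if the nutrient carries none of the effect, and the estimate drops to about 50–78% of the total if it carries 25–50%. At 0.5 SD, selection is only about 27% likely and the SE increase is about 5%.

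The documents do not support the conclusion that the soy milk effect will be adjusted away: that needs diet to be treated as a candidate, to differ between arms and to lie on the causal path. The P < 0.05 screen, the correlations, the shifts and the shares carried are all assumptions. The correction is worth making before the data are seen.

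**What to change.** In the Statistical analysis section, delete the clause that makes adjustment depend on an observed difference between the groups. Specify the main ANCOVA as treatment, baseline value of the outcome, and a short fixed list of pre-randomisation covariates; the matching factors (age, gender, BMI, type of medicines) are the natural candidates. Add that dietary recalls, activity records and compliance do not enter the main model, and are reported descriptively or in a sensitivity analysis labelled as such. Diet is best summarised both with and without the soy milk.

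This needs no extra patients, visits or assays. With one term for each of the four matching factors, residual degrees of freedom go from 30 − 3 = 27 to 30 − 7 = 23, or from 17 to 13 if 10 per arm complete. The only other cost is giving up post-hoc choice of covariates.

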## Discussion

Currently, some medications including amino salicylates, glucocorticosteroids, immune modulators, antibiotics, and anti-TNF drugs are prescribed for IBD patients, which cause severe adverse effects such as increasing anti-antibody reactions, risk of allergy, infection, and mutagenesis [54–56]. Thus, finding a food with therapeutic effects and without toxicity is of great importance for IBD patients. Soy products such as soy milk with anti-inflammatory properties are a good choice for inflammatory diseases including diabetes mellitus and cardiovascular diseases [12, 13, 57]. However, so far, no study has examined the effects of soy milk consumption on inflammatory markers and disease symptoms in patients with IBD. In addition, the beneficial effects of soy milk consumption on gut microbiota have been reported [58]; however, these effects have not been yet assessed in IBD patients. As recently stated, change in the gut microbiota has been a contributing factor to IBD incidence, particularly UC [59–61]. In addition, it has been shown that gut microbiota imbalance can affect disease symptoms [62].

In this study, we hypothesize that soy milk consumption might have a beneficial effect in IBD patients through increasing abundance of beneficial/commensal bacteria and reduction of mucus-degrading taxa. Soy milk contains 0.6 g/100 g fiber which can be considered as a prebiotic [63]. It has long been shown that prebiotics can favorably affect gut microbiota [64]. In an experimental study, soy milk administration resulted in an increase in *Firmicutes* to *Bacteroidetes* ratio in gut microbiota community of rats [58]. Also, soy milk intake had an increasing effect on *Lactobacillus* spp. which potentially protects against gut inflammation [65]. In addition to fiber, protein content of soy milk can affect gut microbial community [66, 67]. In an experimental study on golden Syrian hamsters, soy protein, compared with milk protein, could alter diversity of gut microbial community [68].

Patients with IBD cannot easily tolerate lactose-containing foods such as dairy products [68, 69]. Soy milk as a lactose-free milk might be a good alternative for dairy products in IBD patients. Overall, finding dietary strategies to improve disease severity and symptoms in IBD patients is of high importance. This approach could be much more cost-effective than prescription of medications for long-term use in these patients.

### Strengths

This is the first clinical trial investigating the effects of soy milk consumption on gut microbiota and inflammatory markers in patients with UC. It must be kept in mind that the intervention is of low cost and can easily be carried out in clinical practice. In this study, patients will be block matched with each other in terms of several variables that might influence the eventual findings. Several outcomes including subjective- and objective-based symptoms along with biochemical indicators will be examined in patients at the study baseline and end of trial. Moreover, compliance to the intervention will be assessed throughout the study.

We hypothesize that soy milk consumption can result in decreased inflammation through inducing changes in gut microbial community. Improvement in gut microbiota and inflammatory markers would lead to beneficial effects on disease symptoms and severity as well as quality of life.

### Limitations

Despite using validated questionnaires for assessment of dietary intakes, disease severity, disabilities, and quality of life, misclassification of participants cannot be fully excluded. Furthermore, change in gut microbiota during the sample collection phase is the most important concern for investigators. To avoid this, we will collect fecal samples in the laboratory and keep it immediately at − 70 °C. In addition, we would try our best to have all the fecal samples in the lab within the 2 h after sampling; however, some samples might arrive within > 2 h. One might argue that the sample size would be inadequate for this study; however, it must be kept in mind that several highly cost variables including six inflammatory biomarkers and 9 genes for quantitative real-time polymerase chain reaction (qRT-PCR) are supposed to be quantified in this study. Due to limited funding in developing countries, performing the study with a sample size greater than the one computed for this study would not be affordable for researchers. In addition, most studies on microbiota or fecal calprotectin have been done with a similar sample size [70–73].

## Data Availability

Not applicable

## Abbreviations

IBD: Inflammatory bowel disease
UC: Ulcerative colitis
BMI: Body mass index
CBC: Complete blood count
HADS: Hospital anxiety and depression scale
hs-CRP: Highly sensitive-C reactive protein
TNF-α: Tumor necrosis factor-α
IL-1β: Interleukin-1β
IFN-γ: Interferon gamma
